#### 6.1.3 Other study parameters

In addition, KPS will be recorded in the experimental arm 1 and molecular analysis on prior surgically acquired tumor tissue, as well as at the time of recurrence (if available), will be performed.

### 6.2 Study procedures Arm 1

After obtaining informed consent (for details, see section 9.2), patients will receive treatment and necessary follow-up procedures. During the course of the study, participating centers will collect baseline characteristics, technical data such as MRI's, CT's and treatment plans and date of death. Medical imaging will be uploaded to a radiological database at a FTP server. Central data collection exists of HRQoL assessment, toxicity, anti-edema therapy and performance status. Central data collection will be performed by the study team by phone call, or via digital or paper questionnaires. Study procedures are summarized in Table 3. Patients will complete HRQoL questionnaires and the study team will record toxicity and anti-edema treatment by phone call at baseline and at 2, 4, 6, 13, 26, 39, and 52 weeks from the start of ReRT or until disease progression (whichever is sooner). During the first 6 weeks HRQoL will be assessed using the EQ-5D-5L. At subsequent time points QLQ-C15-PAL and BN20+2 will be completed digitally or on paper. Clinicians will be asked to record toxicity, KPS and anti-edema therapy use during regularly scheduled consults.

In case of suspicion of progression, recurrence or radionecrosis on MRI without consensus of diagnosis by the tumor board a FDG-PET, FET-PET or spectroscopy may be used to differentiate but is not mandatory.

IDH-1/2 mutation and MGMT-methylation will be determined at baseline using prior surgically acquired tissue, when molecular analysis has not been performed before, as well as at the time of recurrence (if available).

Any clinical follow-up data after 12 months will be uploaded at time of death, if known.

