### **8.1.3 HRQoL in arm 1**

HRQoL will only be assessed in the experimental group. Reasons for missing baseline and follow-up questionnaires will be assessed. Linear Mixed Effects models will be used for regression analyses of HRQoL. In addition, the repeated measures of the EQ-5D-5L, QLQ-C15-PAL and BN20+2 functional and symptom scales will be assessed by time to deterioration (TTD) analyses. The time until definitive HRQoL score deterioration (TUDD) is defined as time from inclusion to a first deterioration of the score with a minimal clinically important difference (MCID) of at least 10 points as compared to the baseline score. With no further improvement of more than the MCID as compared to the baseline score or if the patient dropped out after deterioration, resulting in missing data. According to the construction of the HRQoL scores, deterioration corresponds to an increase (e.g., for symptomatic scales of the EORTC questionnaires and EQ-5D-5L) or a decrease (e.g., for functional scales) of the score.

Patients with no score available are excluded from the time-to-deterioration analyses.

Patients with no baseline score are usually censored at baseline and those with no follow up scores but with a baseline score are censored one day after baseline. Patients with no deterioration before drop-out from the study, including death, are censored at the time of last HRQoL questionnaire completion or last follow-up.

The TUDD estimation will be calculated using the Kaplan-Meier method and described using median and 95% CI.

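### Section 8.1.3 allows HRQoL time-to-deterioration to be censored at last follow-up, although questionnaires stop earlier; if that date is used, the deterioration-free curve is biased upward

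*Protocol*

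**What the plan says.** Section 8.1.3 (HRQoL in arm 1) defines the event as a "first deterioration of the score with a minimal clinically important difference (MCID) of at least 10 points as compared to the baseline score", and then: "The TUDD estimation will be calculated using the Kaplan-Meier method and described using median and 95% CI".

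For the rest, it says "Patients with no deterioration before drop-out from the study, including death", "are censored at the time of last HRQoL questionnaire completion or last follow-up". Two dates are joined by *or*, and nothing says when each applies. The same section censors a patient with a baseline score but no follow-up score one day after baseline.

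Section 6.2 (Study procedures Arm 1) schedules questionnaires at baseline and at "2, 4, 6, 13, 26, 39, and 52 weeks from the start of ReRT or until disease progression (whichever is sooner"). The instruments are split over time: "During the first 6 weeks HRQoL will be assessed using the EQ-5D-5L", and "At subsequent time points QLQ-C15-PAL and BN20+2 will be completed digitally or on paper".

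Clinical follow-up runs longer. Section 6.2 has clinical data from after 12 months uploaded at death, and section 4.4 expects up to 3.5 years for some patients. Section 6.6 asks patients withdrawn from treatment to go on with questionnaires; nothing similar is said for patients who progress.

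**The concern.** A drop of 10 points can be recorded only when a questionnaire is completed. After progression, or after the instrument's last scheduled visit, the chance of a recorded event is zero, yet the patient may still be in clinical follow-up. If the later date is the censoring date, that patient stays in the Kaplan-Meier denominator at every later event time and cannot enter the numerator. Each later step is then too small, and time to definitive deterioration (TUDD) looks longer than it is.

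This is separate from the handling of death. The gap arises while patients are alive, so making death a competing event would not remove it.

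Describing HRQoL in the experimental group is a stated secondary objective (section 2.2), and section 1.2 assumes that fewer fractions preserve HRQoL better. The error would favour that assumption, and no control arm has HRQoL data that could reveal it.

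**Working it through.** The protocol gives no TUDD figure, so there is none to reproduce. The check sizes the difference between the two permitted dates.

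**Inputs from the protocol.** Questionnaires at weeks 2, 4 and 6 (EQ-5D-5L) and 13, 26, 39 and 52 (QLQ-C15-PAL, BN20+2), ending at progression (section 6.2). Expected event rate 0.7 at 12 months (section 4.4), so 0.30 alive at week 52.

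**Assumptions not in the protocol.** Median PFS 13, 20 or 26 weeks; true median time to deterioration 26 weeks; exponential times; deterioration independent of progression; follow-up cut at week 52; a baseline score exists for the scale.

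**One case by hand (median PFS 13 weeks, scale measured at weeks 13 to 52).**

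- Progression hazard a = ln 2 / 13 = 0.05332 per week. With post-progression death hazard b, S(t) = (a·e^(−bt) − b·e^(−at)) / (a − b). Setting S(52) = 0.30 gives b = 0.04177, so S(13) = 0.874 and S(26) = 0.654.
- Deterioration-free share per 13 weeks: 0.5^(13/26) = 0.7071.
- Week 13: 0.50 are progression-free; recorded events = 0.50 × 0.2929 = 0.1464.
  - Last questionnaire: 1 − 0.1464/0.50 = 0.707.
  - Last follow-up: everyone alive is at risk, so 1 − 0.1464/0.874 = 0.832.
- Week 26: progression-free and not yet deteriorated = 0.25 × 0.7071 = 0.1768; events = 0.1768 × 0.2929 = 0.0518.
  - Last questionnaire: 0.707 × (1 − 0.0518/0.1768) = 0.50, the true value.
  - Last follow-up: at risk = 0.654 − 0.2929 × (0.50 × 0.874) = 0.526, so 0.832 × (1 − 0.0518/0.526) = 0.75.

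**All three cases (simulation, same model), censoring every deterioration-free patient at last follow-up.**

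| Median PFS | Week 13 (true 0.71) | Week 26 (true 0.50) | Week 39 (true 0.35) | Week 52 (true 0.25) |
|---|---|---|---|---|
| 13 weeks | 0.83 | 0.75 | 0.71 | 0.68 |
| 20 weeks | 0.78 | 0.65 | 0.55 | 0.48 |
| 26 weeks | 0.75 | 0.57 | 0.43 | 0.33 |

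Censoring at the last questionnaire returns the true values in every row. With median PFS 13 weeks, the median is never reached under last follow-up.

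**If the day-one rule is applied scale by scale.** Patients who progress before week 13 have no follow-up score on these scales and would leave the risk set on day one. The week-13 step is then correct (0.7071). With exponential times the later curve is 0.7071 times the tabulated curve one visit earlier:

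- Week 26: 0.7071 × 0.83, 0.78, 0.75 = 0.59, 0.55, 0.53.
- Week 52: 0.7071 × 0.71, 0.55, 0.43 = 0.50, 0.39, 0.30.

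The bias is smaller but keeps its direction.

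**EQ-5D-5L (weeks 2, 4, 6).** At week 6 the curve reads 0.86 to 0.88 instead of 0.85, a shift of about 0.01 to 0.03, and less under the day-one rule. After week 6 it cannot fall. Each deterioration-free patient adds on average about 27 to 29 unobserved weeks, even with follow-up cut at week 52.

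**Does the correction depend on its assumptions?** Take median progression 4 months, post-progression median survival 4.5 months, 3-monthly questionnaires, and a deterioration hazard of 0.10 per month that doubles to 0.20 at progression. The true deterioration-free share is 0.45 at 6 months and 0.16 at 12. Last questionnaire gives 0.55 and 0.30; last follow-up gives 0.74 and 0.65.

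**The case against.** The strongest defence is that the sentence means the last HRQoL contact. Elsewhere in section 8.1.3 follow-up refers to questionnaires, the day-one rule stops counting when scores stop, the sound date is listed first, and the central phone calls in section 6.2 end at progression together with the questionnaires. This is a fair reading, but the text does not fix it. If both phrases meant the same date, the second would add nothing, and section 8.1.4 uses last follow-up as a censoring date for toxicity with no tie to questionnaires. A reader might infer that the plan requires censoring at last clinical follow-up. It does not; it permits it.

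A second defence is that this is detail for the SAP. Section 8.1 does foresee a final SAP and allows minor revisions. But the protocol is not silent here: it names an unsuitable date as acceptable.

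A third is that the EORTC figures may describe an analysis that cannot be run. The Summary and section 6.2 assign baseline and the first 6 weeks to the EQ-5D-5L and start the other instruments afterwards; Table 3 marks HRQoL at baseline without naming an instrument. If those scales have no baseline score, section 8.1.3 would usually censor those patients at baseline and no curve would arise. This stands as a condition on the figures. Section 8.1.3 nevertheless plans TUDD on those scales, so the rule needs to be right once a baseline exists.

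Finally, censoring at the last questionnaire is itself informative if HRQoL falls faster after progression. That stands too: the last example above shows the correction is better but not unbiased.

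**Conclusion.** The rule is ambiguous, and one of its two permitted dates biases the deterioration-free curve upward. The direction follows from the design: time with no measurement is counted as time at risk. The size does not. Values of 0.57 to 0.75 against 0.50 at week 26 and 0.33 to 0.68 against 0.25 at week 52 rest on assumed PFS and deterioration rates, on an EORTC baseline score, and on last follow-up being used for every deterioration-free patient. With the day-one rule applied per scale they fall to 0.53 to 0.59 and 0.30 to 0.50. For EQ-5D-5L the numerical shift is small, and the main fault is a plateau that nobody observed.

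A reader might take these values as a forecast of the trial's results, or think that the main conclusion is at risk. Neither follows. TUDD is descriptive, single-arm and additional to mixed models, with no test or decision attached, and the OS comparison is untouched. The point is still worth correcting, because the error would flatter the experimental schedule and costs almost nothing to remove.

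**What to change.** In section 8.1.3 delete *or last follow-up* and state: *Patients with no deterioration are censored at the date of the last completed questionnaire for that scale.* Show no curve beyond the last scheduled questionnaire for the scale (week 6 for EQ-5D-5L, week 52 for QLQ-C15-PAL and BN20+2). If death or progression is later handled as a competing or composite event, keep this date for all other patients.

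Add as a limitation that censoring at the last questionnaire before progression may still overstate preservation if deterioration speeds up afterwards. Whether the EORTC scales have a baseline score should be settled at the same time, since their TUDD depends on it.

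Cost: three words removed and two or three sentences added, with no new data. The downside is fewer patients at risk at late time points, which reflects what was actually observed.

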### **8.1.4 Toxicity**

Toxicity will only be assessed in the experimental group. Analyses of radiotherapy toxicity will be performed in all patients who received at least one fraction. Acute events occurring from start of radiotherapy until 90 days and late events occurring from 91 days after end of radiotherapy will be presented. Further analyses of treatment toxicity will present the grade 3 to 5 acute or late side effect by treatment arm. The time to occurrence of any severe late side effects and separately radionecrosis (distinguishing symptomatic and asymptomatic) will be estimated by cumulative incidence. The time to severe late side effects will be calculated from the time of start of radiation treatment to the first evidence of any grade 3-5 late side effects. Patients alive without grade 3-5 late toxicity will be censored at the date of last

follow-up, patients who died without experiencing late grade 3-5 side effects will be assessed as competing risk at the time of death.

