## SUMMARY

**Rationale:** Re-irradiation is a generally accepted method for salvage treatment in patients with recurrent glioma. However, no standard radiation regimen has been defined.

Hypofractionation with dose-escalation will reduce patient's burden while maintaining the survival benefit.

**Objective:** To determine if re-irradiation in 4 fractions is non-inferior to 10 fractions in the primary endpoint of survival after re-irradiation. Secondary objectives are to establish and compare recurrence patterns, progression free survival, toxicity and anti-edema treatment and to describe health-related quality of life in the experimental arm.

**Study design:** RISING trial A was an open label, randomized, non-inferiority, phase III trial with 1:1 allocation for 130 patients among all participating centers. RISING trial B will be a phase II, multi-center, clinical trial with a historic control group.

**Study population:** Adults with unifocal recurrent high-grade glioma up to 125 cc eligible for re-irradiation.

**Intervention:** The experimental group receives 4 stereotactic fractions. The historic control group has received 10 fractions (standard of care) with approximately a biological equivalent dose.

**Main study endpoint:** The primary endpoint is overall survival after re-irradiation. The key secondary endpoint is progression free survival. Other secondary endpoints are recurrence patterns, toxicity, HRQoL and anti-edema treatment.

**Nature and extent of the burden and risks associated with participation, benefit and group relatedness:** For the patients included in the study, no individual benefits and no known risks are associated with the tests performed. To reduce patients' burden, hospital visits are mainly limited to standard follow-up. Most additional follow-up assessments will be performed by telephone or by self-administered forms. We use the EQ-5D-5L at baseline and 2, 4 and 6 weeks after start of radiotherapy and thereafter the QLQ-C15-PAL to assess HRQoL. The questionnaires could be conducted in less than 10 minutes at home. Additionally, at the same time points patients will be asked about adverse events, anti-edema treatment and reminded to complete their HRQoL assessments during a phone call of a few minutes. Furthermore, technical data, including MRI, CT and radiation treatment plans, acquired in standard care will be utilized.

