## 1.3 Adverse Events after brain re-irradiation

Adverse events (AEs) in ReRT retrospective studies are often poorly registered and therefore underestimated. Most larger retrospective studies do not report severe acute toxicity or radionecrosis at all [9, 10, 14, 15]. Only few studies, including one phase-I prospective study, reported severe acute toxicity [23, 24]. Some studies reported high rates of radionecrosis, including 30% radionecrosis in the SRT group of the retrospective study of

Cho et al. [25], 36% reported late adverse events in the prospective study by Shepherd et al. [26] and 43% in the minority of patients that were progression-free 10 weeks after treatment in the prospective study of Moller et al. [23]. In the pooled results of a meta-analysis on ReRT in glioblastoma, grade  $\geq 3$  toxicity rates were poorly reported, but considered to be 4-10%, with higher rates in prospective studies [20]. Real difference in toxicity could be assigned to differences in radiotherapy prescription and patient characteristics. However, the large variation among studies is probably for the most part caused by insufficient detection in retrospective studies. It is of great importance to accurately record and analyze AEs after ReRT to assess safety and its influence on HRQoL.

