### 2.2 Secondary Objective(s):

1. To compare progression free survival between the two treatment groups.
2. To describe health-related quality of life (HRQoL) in the experimental treatment group
3. To assess neurocognitive functions in a subgroup of the treatment group.
4. To describe toxicity in the experimental treatment group, and compare grade  $\geq 3$  toxicity in both groups.
5. To establish and compare recurrence patterns on MRI between the two treatment groups.

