## **8.3 Interim analysis**

Six months after inclusion of every 10 patients an interim analysis will be performed to review the toxicity data. If the toxicity is unexpectedly high in large tumors (65-125cc), the maximal tumor diameter will be modified to 5 cm (reflecting a spherical tumor of 65 cc). The detailed interim analyses are not made available to trial participants.

Sequential boundaries will be used to monitor dose-limiting toxicity rate. Full follow-up for acute toxicity is defined as 90 days after last irradiation fraction. Full follow-up for radionecrosis is defined as after the MRI at 6 months. This is a Pocock-type stopping boundary that yields the probability of crossing the boundary at most 0.05 when the rate of dose-limiting toxicity is equal to the acceptable rate 30, 20 or 10% depending on adverse event grading [45].

The research team will be responsible for the interim analysis. The accrual of patients with a tumor with a diameter >5 cm will be halted if excessive numbers of dose-limiting toxicities are seen, that is, if the number of dose-limiting toxicities is equal to or exceeds  $b_n$  out of  $n$  patients with full follow-up (Table 4.1, 4.2 and 4.3). No more interim analyses will be performed if accrual of patients with a tumor volume of >5 cm (reflecting a spherical tumor of 65 cc) is halted based on the above, if after 4 iterations of interim analyses, no excessive numbers of dose-limiting toxicities are seen, as mentioned above or when inclusion is completed without excessive dose-limiting toxicities. In any of these cases, the METC that gave a favorable opinion will be notified.

**Table 4.1 The maximal tumor volume will be modified if the number of dose limiting grade 3 to 5 toxicities is equal to or exceeds  $b_n$  out of  $n$  patients with completed follow-up. This boundary is equivalent to testing the null hypothesis, after each patient, that the event rate is equal to 0.3, using a one-sided level 0.017041 test.**

|                         |    |    |    |    |    |    |    |    |    |    |    |    |    |    |    |    |    |    |    |    |
|-------------------------|----|----|----|----|----|----|----|----|----|----|----|----|----|----|----|----|----|----|----|----|
| Number of Patients, $n$ | 1  | 2  | 3  | 4  | 5  | 6  | 7  | 8  | 9  | 10 | 11 | 12 | 13 | 14 | 15 | 16 | 17 | 18 | 19 | 20 |
| Gr 3-5 Boundary, $b_n$  | -  | -  | -  | 4  | 5  | 5  | 6  | 6  | 7  | 7  | 8  | 8  | 9  | 9  | 10 | 10 | 10 | 11 | 11 | 12 |

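### Section 8.1.4 contradicts the stated toxicity comparison, leaves the end of the acute window unclear, and relies on late-toxicity data whose scheduled collection ends at progression

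*Protocol*

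**What the plan says.** **Scope.** Section 8.1.4 opens with "Toxicity will only be assessed in the experimental group". Three sentences later it says: "Further analyses of treatment toxicity will present the grade 3 to 5 acute or late side effect by treatment arm". Secondary objective 4 in section 2.2 reads "To describe toxicity in the experimental treatment group, and compare grade" 3 or higher in both groups. The Summary agrees: "Secondary objectives are to establish and compare recurrence patterns, progression free survival, toxicity and anti-edema treatment". The heading of section 6.3.2 covers adverse events in arms 1 and 2, recorded or retrieved.

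**Windows.** Section 8.1.4: "Acute events occurring from start of radiotherapy until 90 days and late events occurring from 91 days after end of radiotherapy will be presented". Section 8.3, for interim monitoring: "Full follow-up for acute toxicity is defined as 90 days after last irradiation fraction".

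**Collection.** Section 6.2 schedules study-team calls on toxicity and anti-edema treatment at baseline and at weeks 2 to 52 "from the start of ReRT or until disease progression (whichever is sooner"). The same section asks clinicians to record toxicity at regular consults and states no stop at progression for that route. Section 8.1.4 estimates severe late effects by cumulative incidence. It censors living patients at last follow-up and names death as the only competing event.

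**The concern.** The documents give two incompatible instructions on whether arm 2 toxicity is analysed. Whoever runs the analysis must break either section 8.1.4 or objective 4.

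The choice has consequences. Section 1.3 says that adverse events in retrospective re-irradiation studies are underestimated, and that "the large variation among studies is probably for the most part caused by insufficient detection in retrospective studies". Arm 1 is telephoned at fixed times, while most of arm 2 comes from a retrospective registry. On the protocol's own reasoning, a comparison between the arms would lean against the 4-fraction regimen.

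An unclear acute window means that the same grade 3-5 event could be classed differently by different analysts, or fall in neither class.

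Section 6.1.2 requires agreement that imaging changes are recurrence and not radionecrosis, so the protocol accepts that the two must be actively told apart. The standardised toxicity calls end at that point.

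**Working it through.** No stated sample size, power or error rate bears on this point, so there is no figure of the plan to reproduce.

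**1. Scope, side by side**

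| Place | Arms |
|---|---|
| Summary | compare |
| 2.2, objective 4 | describe in arm 1; compare grade ≥3 in both |
| 6.3.2, heading | arms 1 and 2 |
| 8.1.4, first sentence | arm 1 only |
| 8.1.4, fourth sentence | by treatment arm |

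No reading satisfies every row. Section 4.1 gives the make-up of arm 2: 16 trial A controls plus 83 registry patients make 99, so 83/99 = 84% are retrospective.

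Illustration of the ascertainment effect (assumption, not in the documents): if the true grade ≥3 rate is 10% in both arms and charts miss half, the expected result is 10% in arm 1 against 10% × 0.5 = 5% in arm 2. With the 16 trial A controls fully observed, arm 2 would show (16 × 10% + 83 × 5%)/99 = 5.8%.

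**2. Windows, by day count**

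Let the first fraction be day 0 and the last fraction day D. The late window opens on day D + 91.

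- Acute window counted from the start: days 0 to 90. Unclassified days run from 91 to D + 90, which is D days.
 - Arm 1, all fractions within 2 weeks (Appendix 1.5): D up to 14, so days 91 to 104, up to 14 days.
 - Arm 2, 2 to 3 weeks (sections 3 and 6.1.1): D up to 21, so days 91 to 111, up to 21 days.
- Acute window counted to 90 days after the last fraction, as in 8.3: days 0 to D + 90, so 0 unclassified days in either arm.

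**3. Patients whose calls have ended when the late window opens**

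After a 14-day course the late window opens on day 14 + 91 = 105.

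- Survival: section 4.4 expects 0.7 events at 12 months. Assuming an exponential curve, the share alive at day 105 is 0.3^(105/365) = 0.71.
- Progression-free: the protocol gives no PFS figure. Assuming an exponential curve with median m months, the share is 0.5^(105/(30.44m)).

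| Assumed median PFS | Progression-free, day 105 | Calls ended (progressed or died) | Alive but no longer called |
|---|---|---|---|
| 2.5 months | 38% | 62% | 71% − 38% = 32% (unrounded inputs) |
| 4 months | 55% | 45% | 71% − 55% = 16% |
| 6 months | 67% | 33% | 71% − 67% = 4% |

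PFS counts death as an event, so the third column includes patients who could not have been called anyway. The last column is the group affected by the rule: 4% to 32% of all patients, or 5% to 46% of those alive. Section 1.3 cites one prospective study in which only a minority were progression-free 10 weeks after treatment, which points towards shorter medians in at least one series.

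**The case against.** **On scope.** The first sentence of 8.1.4 may be a slip, since section 8.1.3 opens in the same way for HRQoL, where it is correct. Four places favour a comparison and one does not, so the smallest repair is to correct that sentence. This stands: dropping the comparison is an option, not a necessity. A reader might infer that the protocol itself calls the comparison invalid. It does not: section 1.3 says only that retrospective records under-detect, 16 of the 99 controls come from trial A, and the bias would not hide harm from 4 fractions. Nor should the contrast in section 1.3 between pooled grade ≥3 rates of 4-10% and individual figures of 30-43% be used to size the bias. The outcomes differ, the 30% comes from a retrospective study, and the 43% applies to a progression-free subset.

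**On windows.** The wording can also be read as 90 days after the end of radiotherapy, which closes the gap and matches 8.3. This stands, so the gap is conditional. A reader might also infer that events on days 91 to 104 count nowhere. Even on the gap reading that is not so: 8.3 monitors necrosis, edema and seizures, with acute toxicity counted to 90 days after the last fraction and radionecrosis to the 6-month MRI. Section 8.1.4 also estimates radionecrosis separately, without a day-91 entry rule. Nothing in the document says that radionecrosis begins to appear in those days.

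**On collection.** A reader might infer that all toxicity collection stops at progression, or that late incidence rests only on progression-free patients. Section 6.2 contradicts both. Clinicians record toxicity at consults with no such stop, and clinical data after 12 months are uploaded at death if known. Imaging and information are also uploaded at weeks 26 and 52 (Table 3), and censoring is at last follow-up. What remains is that the standardised route ends. The route left is routine recording, close to the kind of record that section 1.3 distrusts; formal AE reporting ends 30 days after the last fraction (7.2.1).

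**Conclusion.** The scope contradiction is certain and needs correcting, because a stated secondary objective cannot be met under 8.1.4 as written.

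The window defect is real but conditional. The end anchor is unclear and not aligned with 8.3. The gap is up to about 14 days in arm 1 and 21 days in arm 2 if the 90 days run from the start, and zero if they run from the last fraction.

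The collection point holds in a limited form. Standardised ascertainment of late toxicity ends at progression and clinician recording continues, so patients who have progressed stay in the cumulative incidence under weaker observation. The share affected at day 105 (4% to 32% of all patients, alive but no longer called) rests on assumed PFS medians of 2.5 to 6 months and exponential curves. The 10% versus 5% illustration is likewise an assumption.

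These are secondary-endpoint matters; the overall survival analysis is untouched. The toxicity definitions still deserve care, because section 7.4 sets up no DSMB.

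**What to change.** (a) Reconcile 8.1.4 with objective 4, the Summary and 6.3.2. Make arm 1 grade 3-5 rates with 95% confidence intervals the main toxicity result. Then either drop the arm 2 comparison everywhere, or keep it for grade ≥3 as descriptive only, with the under-detection caveat of section 1.3 and with the prospectively followed trial A patients (13 versus 16) shown separately.

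(b) Define acute as first fraction to 90 days after the last fraction, and late as from day 91 after the last fraction, in line with 8.3.

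(c) Continue the already scheduled toxicity and anti-edema calls to week 52 or death regardless of progression, and flag events recorded after progression.

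Cost: (a) and (b) are amendment wording, although (a) gives up a formal between-arm toxicity claim. (c) adds a few short calls for patients who have progressed, a burden that the protocol otherwise tries to limit.

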### 3. STUDY DESIGN

The original 2019 RISING-trial (RISING trial A) was designed as an open label, randomized, non-inferiority, phase III trial with 1:1 allocation for 130 patients. In this trial 13 patients were included in the experimental arm and 16 patients were included in the control arm. The updated 2023 RISinG trial (RISING trial B) is designed as a phase II, multi-center, clinical trial with a historic control group. The additional recruitment period of this phase will be approximately 30 months with an active follow-up time of 12 months.

The 13 patients of the RISING trial A will be supplemented until a total of 66 patients is reached. These patients fulfilling the inclusion criteria will get the following treatment:

- Hypofractionated radiotherapy with SIB in 2 weeks  
4 fractions of 7.5 Gy SIB to the GTV  
And 4 fractions of 5.5 Gy to the CTV (GTV + 5mm margin).

We will compare the survival of this group with a retrospective control group of patients, subtracted from the retro-RISinG registry study, a multi-center retrospective nation-wide population based cohort study, in which details of patient-, tumor- and treatment-related data of all patients with a recurrence of a primary brain tumor since January 2002 up to December 2022 in the Netherlands will be collected. We will select 99 matched patients in total with the following treatment:

- Moderately hypofractionated radiotherapy in 2-3 weeks  
10 fractions of 3.5 Gy to the CTV (GTV + 5 mm margin)

An overview of the target volume definitions and dose prescriptions is presented in table A3 in section 1.8 of the Appendix.

This control group will be matched to the patients in the experimental arm on an individual level for:

1. Age;
2. Gender;
3. WHO-grade primary tumor;
4. Time interval in between first radiation and re-irradiation;
5. MGMT-status.

[figure not shown]

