### 1.5 Prescribed dose and fractionation

The dose prescribed to the PTV in the experimental arm is 4 fractions of 5.5 Gy. The prescribed dose to the PTVboost is 4 fractions of 7.5 Gy. All fractions should be given within 2 weeks. The maximum dose in the PTVboost of the experimental arm should not exceed 130% of the prescription dose. Maximum dose in the PTV should not exceed 107% of the prescription dose according to ICRU rapport 50. The dose calculation grid should be 3 mm or less.

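### Section 8.1.4 closes the acute toxicity window at 90 days without saying after what; counted from the start of radiotherapy, a gap of up to two to three weeks opens before late toxicity begins

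*Protocol*

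**What the plan says.** Section 8.1.4 of the protocol defines both windows together: "Acute events occurring from start of radiotherapy until 90 days and late events occurring from 91 days after end of radiotherapy will be presented". It then plans to show grade 3-5 acute or late effects by arm, and to estimate the time to severe late effects, and separately to radionecrosis, by cumulative incidence.

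Section 8.3, on interim toxicity monitoring, states: "Full follow-up for acute toxicity is defined as 90 days after last irradiation fraction".

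Three other places set the calendar:

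- Appendix 1.5, experimental schedule: "All fractions should be given within 2 weeks".
- Section 3, control schedule: "Moderately hypofractionated radiotherapy in 2-3 weeks".
- Section 6.2, toxicity calls in arm 1: "at 2, 4, 6, 13, 26, 39, and 52 weeks from the start of ReRT".

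**The concern.** The two halves of the sentence in 8.1.4 do not share a reference point. The acute half mentions only the start of treatment; the late half counts from its end. A programmer who applies the only anchor named for acute events stops at day 90 from the first fraction and starts late events on day 91 from the last fraction. The days between belong to no class.

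A grade 3-5 event with onset in those days would be missing from the acute table and, unless it is radionecrosis (estimated separately), from the cumulative incidence of severe late effects. The interim monitoring in 8.3 would treat the same event as falling within acute follow-up, so interim and final acute counts could differ for the same patients. Toxicity is a secondary objective in section 2.2, so the classification rule should be unambiguous.

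**Working it through.** The protocol gives no figure for this point, so there is none to reproduce. The check is day counting.

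**Inputs.** Day 0 is the first fraction and T is the day of the last fraction.

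- Acute window, 8.1.4: "Acute events occurring from start of radiotherapy until 90 days".
- Late window, 8.1.4: "late events occurring from 91 days after end of radiotherapy will be presented", that is, from day T + 91.
- Acute follow-up, 8.3: complete at day T + 90.
- Arm 1 (Appendix 1.5): at most 2 weeks, so T is at most 13 or 14. T = 13 if the first fraction counts as the first of 14 calendar days; T = 14 if two full weeks may elapse.
- Arm 2 (section 3): 2-3 weeks, so T is at most 20 or 21 on the same two conventions.
- Week 13 (section 6.2): 13 × 7 = day 91.

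**Reading A: the 90 days count from the start.** Acute is days 0 to 90 and late begins at day T + 91. The unclassified days run from 91 to T + 90, and their number is (T + 90) − 91 + 1 = T.

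| Arm | T | Unclassified days | Length |
|---|---|---|---|
| 1 | 13 | 91-103 | 13 |
| 1 | 14 | 91-104 | 14 |
| 2 | 20 | 91-110 | 20 |
| 2 | 21 | 91-111 | 21 |

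These are upper bounds. If the four fractions were given on consecutive days (an assumption), T = 3 and the gap is 3 days (91-93).

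**Reading B: the 90 days count from the last fraction, as in 8.3.** Acute is days 0 to T + 90 and late begins at T + 91. The gap is (T + 91) − (T + 90) − 1 = 0 days for every T in either arm.

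**Week 13.** Day 91 is the first unclassified day under Reading A for any T of at least 1. Under Reading B it is acute, because 91 ≤ T + 90.

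**Difference between arms, Reading A only.** At the stated durations of 2 weeks against 2-3 weeks, the control gap is longer by 14 − 14 = 0 to 21 − 14 = 7 days. It is longer still if the four fractions finish in under 2 weeks. Ten weekday fractions starting on a Monday (an assumption) give T = 11, which is 3 days shorter than an arm 1 course with T = 14.

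**Example.** Take a grade 3 seizure with onset on day 95 in a patient with T = 13. By 8.3, acute follow-up runs to day 103; seizures are among the monitored terms, so the event could count towards the Table 4.1 boundary if judged related to radiotherapy. By Reading A of 8.1.4, acute ended on day 90 and late begins on day 104, so the event is in neither class.

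**The case against.** The strongest reply is that no gap was intended. The consecutive numbers 90 and 91 suggest adjoining windows, with the end of radiotherapy as the reference for both, and 8.3 supports this. That is a reasonable reading, and it stands: a reader might infer that the protocol definitely leaves days unclassified, but the text does not establish this. It leaves the reference point open.

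Three further inferences go too far.

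- **That the week-13 assessment is lost.** Section 8.1.4 classes events by when they occur. An event with onset by day 90 that is reported at the week-13 call remains acute, and section 6.2 also has clinicians record toxicity at regular consultations. What remains is narrower: no call is scheduled between day 42 (week 6) and day 91, and 8.1.4 times severe late effects to first evidence. An event first noted at that call could therefore be dated day 91 unless onset is recorded.
- **That the gap is longer for controls and distorts the comparison.** The stated durations overlap at 2 weeks, so it is only possibly longer. It also matters only if toxicity is compared between arms. On that, 8.1.4 is inconsistent: it says "Toxicity will only be assessed in the experimental group" and then presents severe effects by arm, while section 2.2 plans a comparison.
- **That every severe event in the gap disappears from the analysis.** Radionecrosis is estimated separately, and nothing in 8.1.4 expressly confines it to the late window.

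It can also be said that an exact day anchor could wait for the final statistical analysis plan. However, the protocol has already fixed the windows, names only the start for one and the end for the other, and uses the last fraction in 8.3. A later plan would have to choose between two texts of the same protocol.

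**Conclusion.** The point holds as a missing reference point in 8.1.4, with a conditional consequence. If the 90 days are counted from the start of radiotherapy, the unclassified period equals the treatment duration, up to about 13-14 days in arm 1 and 20-21 days in arm 2, and the acute window disagrees with 8.3. If they are counted from the last fraction, there is no gap, but 8.1.4 does not say so.

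The effect is limited to the acute or late label of grade 3-5 events with onset from day 91 to at most day 111, and to whether they enter the late cumulative incidence. The number is probably small; the protocol gives no event rate for this period, so it cannot be calculated. Overall survival and progression-free survival are unaffected. The upper bounds assume treatment takes the full stated time. The correction is worth making because the ambiguity touches a stated safety objective and is easily removed.

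**What to change.** In section 8.1.4, define acute toxicity as onset from the first fraction through day 90 after the last fraction, and late toxicity as onset from day 91 after the last fraction onward. This matches 8.3 and closes the gap for every treatment duration. Apply the same definition wherever arms are presented, and classify each event by its onset date, not by the date of the call or visit at which it was reported. The time origin for severe late effects can remain the start of radiotherapy.

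The cost is one sentence in 8.1.4. The visit schedule, the sample size and the interim boundaries do not change. Onset dates need to be recorded for grade 3-5 events if they are not already.
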